### Data collection

Participants have data collected from their routine care records, for assessments as shown in Additional file 3: Table S1.

Data collection continues from day 1 to 21 days after randomisation or until death if earlier. Daily assessments stop at day 14, or earlier if the participant is discharged from the ICU/CCU or dies before day 14. For participants discharged home prior to 21 days post-randomisation, a brief telephone interview is conducted between days 20 and 24, providing consent is given. The condition of participants still in hospital at 21 days is assessed from their notes. A medical record check is carried out for the participant’s final date of discharge, or death noted up to day 28.

Study data are collected and managed using REDCap [18, 19] electronic data capture tools hosted at the Norwich Clinical Trials Unit (NCTU). Research Electronic Data Capture (REDCap) is a secure, web-based software platform designed to support data capture for research studies, providing audit trails for tracking data manipulation and export procedures and automated export procedures for seamless data downloads to common statistical packages.

### Adverse event reporting and monitoring

Adverse events (AEs) and serious adverse events (SAEs) that are secondary outcomes in the trial do not need to be reported in an expedited manner but are recorded in the database. Machine and laboratory errors or issues producing misleading or wrong results, leading to ineffective therapy with potential or actual serious consequences, are to be reported immediately as SAEs. Such errors may occur as a result of technical problems or by limitations of the design (e.g. organisms not present on the panel or specific laboratory reporting practices). In addition, investigators may report other relevant events.

An independent Data Monitoring Committee (DMC) has oversight of all trial safety data and can make recommendations as required. No interim analyses are planned.

Adherence to the protocol is monitored throughout, as are data quality and completeness.

### Outcomes

The trial has co-primary outcomes of the following:
Non-inferiority in clinical cure of pneumonia at 14 days post-randomisation. Cure of pneumonia is defined as follows: absence of (i) death where pneumonia was considered causative or contributory; (ii) septic shock, except when associated with a documented non-respiratory origin of infection; (iii) relapse of pneumonia (relapse is defined as an infectious pulmonary event, associated with clinical and radiological signs of HAP or VAP, or a worsening of 2 points of the baseline multiple organ dysfunction score (SOFA or PELOD-2)); or (iv) other evidence that the original pneumonia is not cured.Superiority in antimicrobial stewardship at 24 h post-randomisation is defined as participants on active and proportionate antimicrobial therapy within 24 h of clinical diagnosis, where active therapy is defined as receiving an antimicrobial active against the organism(s) in vitro and proportionate as active and not excessively broad spectrum for the pathogen(s) identified.

The secondary outcomes comprise the following:
(i)ICU/CCU length of stay, calculated as the time from randomisation to discharge from the ICU/CCU(ii)Number of ventilator-free days within 21 days post-randomisation(iii)Mortality, calculated as deaths from any cause within 28 days of randomisation(iv)Incidence of septic shock within 21 days of randomisation(v)Change in SOFA (ΔSOFA) score from randomisation to 7 days post-randomisation for adults(vi)Change in PELOD-2 (ΔPELOD-2) score from randomisation to 7 days post-randomisation for children(vii)Change in pSOFA (ΔpSOFA) score from randomisation to 7 days post-randomisation for children(viii)Proportion of participants on antibiotics active/inactive against the pathogen(s) found at 24 and 72 h from randomisation(ix)Proportion of participants on proportionate/disproportionate antibiotics, in relation to pathogen(s) found at 72 h from randomisation(x)Proportion of participants on narrow-spectrum antimicrobials at 24 and 72 h from randomisation(xi)Proportion of participants with specific adverse events associated with antibiotics within 21 days from randomisation(xii)Proportion of participants contracting a secondary pneumonia within 21 days from randomisation(xiii)Total per patient antibiotic usage in defined daily doses (DDDs) by 21 days post-randomisation (all conditions)

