## Objectives

The overall trial aim is to show that clinical and safety outcomes for patients whose treatment is guided by the FilmArray test molecular diagnostic are non-inferior compared to standard care, but that altered prescribing leads to improved antimicrobial stewardship.

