## Methods/design

### Design

INHALE WP3 is a multi-centre, open-labelled, parallel, randomised controlled trial exploring the potential impact of the FilmArray rapid molecular diagnostics coupled with a prescribing algorithm, aiming for non-inferiority in clinical cure of pneumonia and superiority with regard to antimicrobial stewardship, compared with standard care. Additional file 1: Figure S1 illustrates the design. Participants are randomised in a 1:1 ratio centrally, via a Research Electronic Data Capture (REDCap) [18, 19] web-based randomisation system, to receive either the intervention plus standard care or standard care alone. Randomisation is stratified by site using permuted block allocation of randomly varying block lengths; concealment of allocation is guaranteed by using the web-based system. All participants remain in the trial for up to 28 days for data collection. Once a participant is randomised, the trial is open-label, meaning clinicians and all study team members will know which group a participant is in. The participant will also be informed upon request. Outcome assessors of the superiority co-primary outcome will remain blinded to the treatment group, and there are no circumstances under which allocation will be revealed to them.

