### Analysis

The co-primary outcomes will be summarised as the proportion of participants where:
Clinical cure was achieved by 14 days after randomisation;Active and proportionate antimicrobial therapy has been initiated within 24 h of randomisation.

For both outcomes, the effect of the intervention will be described using a difference in proportions, and an odds ratio, each calculated with a 95% confidence interval. For the non-inferiority analysis of clinical cure, confidence intervals will be one-sided. Estimates will be obtained from regression models that allow for study site. Similar approaches will be used for binary secondary outcomes. For continuous secondary outcomes, the groups will be compared using standard regression models (where normality assumptions are satisfied) to obtain the differences in the means allowing for site and adjusting for baseline values where these are available.

In all superiority analyses, participants will be analysed on an intention-to-treat basis, regardless of clinicians’ decisions in using the FilmArray test results and the associated algorithm, or in respect of the antibiotics prescribed. A Microbiology Committee, comprising three independent members and one member of the study team, has been set up to review the prescribing decisions. The committee assesses whether prescribing is active and proportionate at 24 h and 72 h post-randomisation for each patient and is blinded to the study arm. Per-protocol analysis will provide the primary results for the non-inferiority outcome. The committee Terms of Reference are shown [see Additional File 4].

Data analysts will not be blinded. A detailed statistical analysis plan will be finalised before analysis and will include details of any relevant sub-group or adjusted analyses. It will be made available, upon request, from the Trial Management Group.

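### Clinical cure can include patients who died by day 14 of causes not attributed to pneumonia, and two of its components conflict over non-respiratory deterioration

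*Protocol article*

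**What the plan says.** The Outcomes section of the protocol article defines cure of pneumonia at 14 days as the absence of four things:

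- (i) death, but only in this form: "absence of (i) death where pneumonia was considered causative or contributory";
- (ii) shock, worded with one exemption: "septic shock, except when associated with a documented non-respiratory origin of infection";
- (iii) a relapse, meaning an infectious pulmonary event with clinical and radiological signs, "or a worsening of 2 points of the baseline multiple organ dysfunction score (SOFA or PELOD-2");
- (iv) "other evidence that the original pneumonia is not cured".

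All-cause mortality is a separate secondary outcome at 28 days. Under Primary objectives, success depends on the two co-primary outcomes only.

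On blinding, the Design section says that after randomisation "the trial is open-label, meaning clinicians and all study team members will know which group a participant is in". The only blinding it promises is this: "Outcome assessors of the superiority co-primary outcome will remain blinded to the treatment group". The Analysis section gives the blinded Microbiology Committee's remit: "The committee assesses whether prescribing is active and proportionate at 24 h and 72 h post-randomisation for each patient and is blinded to the study". Cure and cause of death are not mentioned there.

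The overall aim under Objectives is that "clinical and safety outcomes for patients whose treatment is guided by the FilmArray test molecular diagnostic are non-inferior".

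**The concern.** There are two separate problems.

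**Deaths.** A death by day 14 in which pneumonia is judged to have played no part is a cure unless (ii), (iii) or (iv) happens to apply. That judgement is subjective, and nothing in the article shields it from knowledge of allocation. In a non-inferiority comparison, an excess of such deaths on the intervention arm, or a tendency to attribute deaths there to other causes, pushes towards declaring success. All-cause mortality does not enter the decision.

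**Internal conflict.** Component (ii) excuses shock with a documented source outside the lung. The organ-score clause in (iii) is joined by "or" and carries no such exemption. A patient with excused shock would usually worsen by 2 points and fail anyway. If the literal reading is applied, failures unrelated to pneumonia occur in both arms and pull the cure rates together, which also favours non-inferiority.

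**Working it through.** **Inputs from the article (Sample size, Analysis, Design):** cure 55% in both arms, margin 13 points, one-sided 95% interval for cure, 1:1 allocation, 552 patients, 5% attrition. Evaluable per arm: 552 × 0.95 / 2 = 262.

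**Assumed, because the article gives no figure:** the share of deaths not attributed to pneumonia, the amount of misattribution, and the rate of unrelated organ-score worsening.

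**Formula.** With control cure pc, intervention cure pt, deficit D = pc − pt and SE = √[pc(1−pc)/262 + pt(1−pt)/262]:

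P(declare non-inferiority) = Φ((0.13 − D)/SE − 1.645).

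**1. The plan's own figure.** At 55% v 55%, SE = 0.0435 and Φ(0.13/0.0435 − 1.645) = 0.911. The stated 91% reproduces. At one-sided 2.5% the result would be 84.9%, so the plan used one-sided 5%.

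**2. Attribution shift at the margin.** True cure is 42% v 55%, where false non-inferiority is 5%. Move s points of intervention-arm failures to cured:

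| s | patients (s × 262) | pt v pc | false non-inferiority |
|---|---|---|---|
| 1 point | about 3 | 43 v 55 | 7.9% |
| 2 points | about 5 | 44 v 55 | 11.8% |
| 3 points | about 8 | 45 v 55 | 17.0% |

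For s = 2: SE = 0.0434 and Φ(0.02/0.0434 − 1.645) = 0.118.

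**3. Excess deaths not counted.** Cure as written is 55% in both arms, so the declaration rate stays at 91%. Suppose the intervention arm has 5 points (about 13 patients) more deaths not attributed to pneumonia, and these were counted as failures. At 50 v 55, SE = 0.0436 and Φ(0.08/0.0436 − 1.645) = 0.576. If controls also had 5% or 10% of such deaths (45 v 50, or 40 v 45), the result is 0.576 or 0.583. For a 2-point excess it is 0.811. All of these assume that none of the excess deaths already fails under (ii) to (iv).

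**4. Organ-score failures unrelated to pneumonia.** Suppose 15% of true cures fail this way in both arms. Then 55% becomes 0.55 × 0.85 = 46.75% and 42% becomes 0.42 × 0.85 = 35.7%. The deficit shrinks from 13 to 11.05 points, SE = 0.0427, and false non-inferiority is 0.117.

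**5. Price of an all-cause primary definition.** By the same logic, if 5% of true cures die of unrelated causes in both arms, the rates are 52.25% v 39.9%, the deficit is 12.35 and false non-inferiority is 6.8%. If 10%, they are 49.5% v 37.8%, the deficit is 11.7 and false non-inferiority is 9.0%.

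**6. Power.** With equal arms at 50% or 45% cure, power is 90.8% or 91.1%. Counting these deaths as failures in both arms barely affects it.

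**The case against.** Several points on the other side stand.

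- A reader might infer that every death from another cause counts as cured. The text does not say that. Component (i) reaches deaths to which pneumonia merely contributed, (iv) is a broad catch-all, and (ii) and (iii) will catch further deaths. Patients not expected to survive 48 h are excluded at entry. The gap is a residual group of unknown size.
- The two problems cannot both be present at full size. If any 2-point worsening is a failure, most patients who deteriorate and die already fail under (iii). If the clause is tied to a pulmonary event, step 4 falls away and the death gap widens. Steps 3 and 4 are therefore alternatives and must not be added.
- A reader might infer that the article states unblinded attribution of cause of death. It does not say who makes the judgement. Open attribution follows from the Design section, but the full protocol, not shown, may provide adjudication. That would answer the attribution concern only. It would not change the rule that such a death can be a cure.
- Excess deaths would not be invisible: 28-day all-cause mortality is reported and an independent monitoring committee sees the safety data. Neither enters the non-inferiority decision.
- The outcome is named as cure of pneumonia, and a pneumonia-specific definition is a recognisable choice. Replacing it with all-cause death has its own dilution cost (step 5). The material does not show that the primary definition must be replaced.

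**Conclusion.** The concern holds in limited form. Under the written definition, a patient dead by day 14 with pneumonia judged neither causative nor contributory, and with none of (ii) to (iv), is cured; the article states no blinded assessment of that judgement. Components (ii) and (iii) conflict on their literal wording.

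The size is conditional on the assumed rates. False non-inferiority at the margin goes from 5% to about 12% if 2 points are reattributed wholly in the intervention's favour, or to about 12% if 15% of true cures fail on unrelated organ-score worsening. A 5-point excess of uncounted deaths leaves the declaration rate at 91% instead of 58%; this is an upper bound, since some of those deaths would fail under another component. The article has no data that would make any of these scenarios likely or unlikely.

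**What to change.** 1. **Reconcile (ii) and (iii).** Either count the organ-score worsening only when it accompanies an infectious pulmonary event, or exempt it when a non-respiratory cause is documented.
2. **Add a key supplementary non-inferiority analysis,** pre-specified with the same 13-point margin, in which death from any cause by day 14 is non-cure. Report it beside the primary result, and require the two to agree before clinical non-inferiority is claimed without qualification.

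Making all-cause death the primary definition is an option. Its downside is the dilution in step 5: false non-inferiority of about 7% to 9% if 5% to 10% of true cures die of unrelated causes in both arms.

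Cost: wording and one added analysis. Deaths are already recorded to day 28, and power stays at about 91% for cure rates from 45% to 55%, so the sample size need not change.

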### Sample size

The trial aims to recruit 552 patients over a 24-month recruitment period. Calculation of the required sample size is based on the co-primary outcomes of clinical cure at 14 days and antimicrobial stewardship at 24 h. The trial will investigate non-inferiority in terms of clinical cure and superiority for antimicrobial stewardship. Calculations aim to achieve 90% power and 5% significance for the co-primary analyses and allow for up to 5% attrition. Data for the first 100 patients from work package 2 provide estimates for the sample size calculation. For the non-inferiority outcome, a clinical cure rate of 55% is assumed in both trial arms, and the non-inferiority limit is defined to be 13% [23–27]. Under standard care, it was estimated that 53% of patients received antibiotics that were both appropriate and proportionate within 24 h of clinical diagnosis, and it is clinically important to improve this by at least 20% (to 73%). The planned sample size of 552 patients will provide 91% power for the non-inferiority outcome analysis and 99% power for the superiority outcome, resulting in 90% for the co-primary analysis (0.91 × 0.99 = 0.9), under the conservative assumption of no correlation between the outcomes [28]. The sample size is not inflated for non-compliance, as none is expected.

The estimates used for both cure rate and antimicrobial stewardship are consistent with those reported in published studies [24–30].

The trial originally aimed to recruit 466 participants, but this was updated to 552 to reflect an expected lower estimated cure rate for pneumonia among COVID-19 patients (postulated at the time to be between 20 and 40% vs. an original estimate, pre-COVID, of 70%). Assuming a maximum of 30% of the final sample might be COVID-19 patients, the minimum expected overall cure rate is 55%, as used in the new sample size calculation. Estimates were based on the data already collected and decided in consultation with the principal investigators.

### Analysis

The co-primary outcomes will be summarised as the proportion of participants where:
Clinical cure was achieved by 14 days after randomisation;Active and proportionate antimicrobial therapy has been initiated within 24 h of randomisation.

For both outcomes, the effect of the intervention will be described using a difference in proportions, and an odds ratio, each calculated with a 95% confidence interval. For the non-inferiority analysis of clinical cure, confidence intervals will be one-sided. Estimates will be obtained from regression models that allow for study site. Similar approaches will be used for binary secondary outcomes. For continuous secondary outcomes, the groups will be compared using standard regression models (where normality assumptions are satisfied) to obtain the differences in the means allowing for site and adjusting for baseline values where these are available.

In all superiority analyses, participants will be analysed on an intention-to-treat basis, regardless of clinicians’ decisions in using the FilmArray test results and the associated algorithm, or in respect of the antibiotics prescribed. A Microbiology Committee, comprising three independent members and one member of the study team, has been set up to review the prescribing decisions. The committee assesses whether prescribing is active and proportionate at 24 h and 72 h post-randomisation for each patient and is blinded to the study arm. Per-protocol analysis will provide the primary results for the non-inferiority outcome. The committee Terms of Reference are shown [see Additional File 4].

Data analysts will not be blinded. A detailed statistical analysis plan will be finalised before analysis and will include details of any relevant sub-group or adjusted analyses. It will be made available, upon request, from the Trial Management Group.

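### The stated model for clinical cure allows for site only, although the sample-size revision assumes a 30 to 50 point cure gap by COVID-19 status; adding that covariate would gain precision

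*Protocol article*

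**What the plan says.** The Analysis section describes both co-primary outcomes by a difference in proportions and an odds ratio with 95% confidence intervals, and adds: "Estimates will be obtained from regression models that allow for study site". For cure, "For the non-inferiority analysis of clinical cure, confidence intervals will be one-sided", and the per-protocol analysis is primary. Baseline adjustment is mentioned only for continuous secondary outcomes. The Design section names site as the sole stratification factor. Any relevant adjusted or sub-group analyses are left to a statistical analysis plan (SAP) to be finalised before analysis.

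The Sample size section gives cure among COVID-19 patients as "postulated at the time to be between 20 and 40% vs. an original estimate, pre-COVID, of 70"%. It continues: "Assuming a maximum of 30% of the final sample might be COVID-19 patients", which leads to a minimum overall cure rate of 55%. The resulting design: "a clinical cure rate of 55% is assumed in both trial arms, and the non-inferiority limit is defined to be 13" points. The stated result is that 552 patients "will provide 91% power for the non-inferiority outcome analysis and 99% power for the superiority outcome".

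**The concern.** The variable that drove the increase from 466 to 552 does not appear in the model stated for the outcome it affects. On the protocol's own figures it separates patients whose cure rates differ by 30 to 50 points. If it is omitted, the variation between these two groups stays in the error term. A chance difference in COVID-19 share between the arms then also carries straight through to the estimated difference in cure. Stratifying by site balances COVID-19 only as far as it tracks site. At stake is precision in a non-inferiority test planned with only one point of power to spare; the validity of that test is not in question.

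**Working it through.** **Inputs.** From Sample size: N = 552; 5% attrition, so about 524 evaluable or 262 per arm; cure 55% in both arms; margin 13 points; COVID-19 cure 20 to 40%; other patients 70%; COVID-19 share at most 30%. From Analysis: one-sided 95% interval for cure, so one-sided α = 0.05 and z = 1.645. Assumptions of this check: 70% applies to all non-COVID patients, all 262 per arm enter the cure analysis, and a 10% share serves as a lower scenario.

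**1. Reproduce the stated power.** Power = Φ(0.13 / √(2v/262) − 1.645), with v = p(1 − p).
- v = 0.55 × 0.45 = 0.2475; standard error √(2 × 0.2475/262) = 0.0435; Φ(2.991 − 1.645) = 91.1%, against 91% stated.
- The 55% is itself the worst-case mixture: 0.3 × 20% + 0.7 × 70% = 55%.
- Superiority (53% vs 73%, two-sided 5%) gives 99.8%, against 99% stated.

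**2. Adjust for COVID-19 status.** Replace v by the within-group variance, the share-weighted sum of p(1 − p).
- *30% share, COVID-19 cure 20%:* 0.7 × 0.21 + 0.3 × 0.16 = 0.195. The variance falls by 0.0525/0.2475 = 21%. Power = Φ(3.370 − 1.645) = 95.8%. In precision this is worth about 552/0.788 ≈ 700 patients without adjustment.
- *30% share, COVID-19 cure 40%:* overall cure 61%, v = 0.2379 unadjusted and 0.7 × 0.21 + 0.3 × 0.24 = 0.219 adjusted. The variance falls by 8%; power goes from 92.0% to 93.8%.
- *10% share (assumed):* power goes from 93.0% to 95.0% at 20% cure, and from 93.6% to 94.3% at 40%.

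**3. Chance imbalance.** At a 30% share, the standard deviation of the between-arm difference in COVID-19 share is √(2 × 0.3 × 0.7/262) = 4.0 points. Multiplied by the cure gap, this adds a component with a standard deviation of 2.0 points (50-point gap) or 1.2 points (30-point gap) to the unadjusted difference. This is the same variance that step 2 removes, seen another way, and not an additional loss.

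**4. Error rate at the margin.** In simulation (40,000 trials), with an 18.6-point deficit in non-COVID patients only, the overall difference is −0.7 × 18.6 = −13.0 points. Non-inferiority is declared in 5.1% of trials unadjusted and 4.9% adjusted, so both hold the 5% level.

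**5. Does adjustment show whether the effect differs by COVID-19 status?** Take a 13-point deficit in non-COVID patients, none in COVID-19 patients, a 30% share and 20% COVID-19 cure (all assumed for illustration). The crude and adjusted differences both average −0.7 × 13 = −9.1 points. Non-inferiority is declared in 23% of trials unadjusted and 25% adjusted. An interaction test has 37% power. A separate non-COVID estimate meets the margin in about 5% of trials at that deficit, and in about 86% when the arms are equal.

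**The case against.** The strongest reply is that the protocol leaves adjusted and sub-group analyses to the SAP, which is not shown, and that the sentence quoted never says site alone. This limits the weight of the point, because the protocol does not exclude a COVID-19 covariate. It does not remove the point: the sentence states how the co-primary estimates will be obtained and names one factor. The deferred adjusted analyses read more naturally as additions to that estimate.

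A second reply is that nothing is broken. That is right: the planned power is met and the error rate holds. The largest gain also needs both the maximum share and the lowest postulated cure rate, and site may already carry part of the COVID-19 variation.

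Three stronger readings are tempting, and the protocol supports none of them.
- *That adjustment would reveal a deficit masked by COVID-19 patients.* Step 5 shows that it would not: a main effect still yields one averaged difference. The premise that cure in these patients depends little on antibiotic choice is also not in the text. The Eligibility criteria admit them only when antibiotics are started or changed for suspected secondary bacterial infection.
- *That the stewardship model needs the same covariate.* The COVID-19 figures concern cure only, and superiority power is already 99.8%.
- *That the change is free.* The planned odds ratio is non-collapsible, so adjustment changes what it estimates. The article also does not show that COVID-19 status is recorded at baseline.

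**Conclusion.** The point holds as a recommendation on efficiency for the cure outcome. On the protocol's own figures, omitting COVID-19 status from the primary cure model forgoes about 2 to 5 points of non-inferiority power at the 30% maximum share, and about 1 to 2 points at an assumed 10% share. These are upper figures, calculated before any variation that site absorbs. They rest on the postulated cure rates, equal cure in the two arms and 262 analysed per arm. A reader should not infer that the planned test is invalid or falls short of its stated power.

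**What to change.** In the primary model for clinical cure, add COVID-19 status at randomisation to site, after confirming that it is recorded at baseline. Report the marginal risk difference by standardisation, with its one-sided 95% interval, so that the 13-point margin still applies. State that the odds ratio is then conditional on the covariates, or standardise it as well.

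Separately, and as a supportive analysis only, have the SAP give the risk difference in cure among non-COVID patients with its confidence interval. Leave the stewardship model as it stands.

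The cost is a few lines of wording, fixed before analysis (the article says the analysts will not be blinded), plus a standardisation step and a note on the odds ratio. No additional patients are needed.

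### ICU stay and total antibiotic use are compared as mean differences, but their definitions give death no place, so excess early deaths could lower both without any benefit

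*Protocol article*

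**What the plan says.** The Analysis section of the protocol article sets one approach for secondary outcomes on a continuous scale: "the groups will be compared using standard regression models (where normality assumptions are satisfied"). The reported effect is a mean difference between arms that accounts for site, and for the baseline value when one exists. The section does not say what replaces this model when normality fails.

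The Outcomes section defines the variables concerned:

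- "ICU/CCU length of stay, calculated as the time from randomisation to discharge from the ICU/CCU"
- "Total per patient antibiotic usage in defined daily doses (DDDs) by 21 days post-randomisation (all conditions")
- Change in SOFA "score from randomisation to 7 days post-randomisation for adults", with PELOD-2 and pSOFA treated the same way in children.

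The Data collection section adds two limits. The first is on overall follow-up: "Data collection continues from day 1 to 21 days after randomisation or until death if earlier". The second is on the day-by-day measurements, which can end sooner still because leaving the ICU also stops them: "Daily assessments stop at day 14, or earlier if the participant is discharged from the ICU/CCU or dies before day 14". The section also describes a record check for final discharge or death up to day 28.

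Death is counted elsewhere. The secondary outcomes include "Mortality, calculated as deaths from any cause within 28 days of randomisation", and a pneumonia-related death counts as failure in the clinical cure co-primary.

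**The concern.** A patient who dies on day 3 stops accruing DDDs on day 3. The outcome is a total per patient, not a rate per day alive, so each additional early death pulls the mean down. A lower mean would be read as reduced antibiotic use.

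ICU stay has the same weakness if death in the ICU is taken as the end of the stay. If such patients are instead left out because they were never discharged, the comparison is confined to survivors, a group formed after randomisation.

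Day-7 organ dysfunction raises a different question. No value exists after death, and daily assessments stop at ICU discharge, so the comparison may rest on a selected subset.

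The direction matters in this trial. The Background section names under-treatment as a cause of death and says that restrictive stewardship may deny seriously ill patients effective therapy. The algorithm favours narrow-spectrum agents. If that harm occurred, it would push two named secondary outcomes the favourable way.

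**Working it through.** **The plan's own figures.** The article gives no figure for these secondary outcomes. Its sample size concerns only the co-primaries and reproduces: 552 × 0.95 = 524.4 patients; SE = √(2 × 0.55 × 0.45 / 262.2) = 0.0435; 0.13/0.0435 − 1.645 = 1.35, which gives 91% power as stated. Nothing below changes it.

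**Inputs.** Mortality, mean stay and DDDs per day are not in the article. All values below are assumptions, shown as ranges.

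**Closed form.** Suppose the intervention changes nothing except to move a fraction e of patients from survivor to early death, and death ends the stay:

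shift in mean = −e × (mean in survivors − mean in deaths)

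| Assumed mean stay, survivors / deaths (days) | Stay, e = 0.05 | Stay, e = 0.10 | DDDs, e = 0.05, at 1.0 and 1.5 per day |
|---|---|---|---|
| 10 / 4 | −0.05 × 6 = −0.30 | −0.60 | −0.30, −0.45 |
| 14 / 5 | −0.05 × 9 = −0.45 | −0.90 | −0.45, −0.68 |
| 20 / 7 | −0.05 × 13 = −0.65 | −1.30 | −0.65, −0.98 |

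**Simulation.** There were one million patients per arm and no effect on recovery.

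- ICU time is log-normal with median 12 days and is not capped at day 28.
- The daily death hazard is 0.010 and rises with severity. The intervention arm has extra hazard in days 0 to 7 only.
- Antibiotic use is 1.3 DDDs per ICU day alive, up to day 21.

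| 28-day mortality, control / intervention | Stay, death ends it | Stay, discharged alive only | DDDs | Change in SOFA, alive at day 7 |
|---|---|---|---|---|
| 27.8% / 27.8% (no harm) | −0.03 | −0.03 | −0.02 | −0.002 |
| 27.8% / 30.3% | −0.47 | −0.11 | −0.50 | −0.028 |
| 27.7% / 32.9% | −0.85 | −0.14 | −0.94 | −0.059 |
| 27.7% / 37.5% | −1.63 | −0.31 | −1.81 | −0.117 |

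The first row shows the random error of the simulation, about 0.03 day.

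**Reading the results.** For about 5 points of excess early mortality, the two methods together give a stay shorter by 0.3 to 0.9 days and DDDs lower by 0.3 to 1.0, with no benefit behind either. Restricting stay to patients discharged alive cuts the shift to about 0.1 day. The SOFA shift among patients alive at day 7 is small.

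**The case against.** The strongest reply is that a reader might infer from this that the plan ignores death. The article does not say so; it is silent. It condenses a full protocol and defers detail to a statistical analysis plan, neither of which is shown, and either may set the rule. That stands, and it limits the point to what the article does fix: a difference in means, applied to definitions in which death has no place. An analysis plan that followed those definitions literally would carry the problem forward.

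Second, the mean-difference model applies only where normality holds, and ICU stay and DDDs are often skewed. That also stands, so the article may not commit to this model for them. But the condition concerns the shape of the distribution; a model chosen for skewness would not by itself deal with death.

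Third, harm would not be hidden. All-cause 28-day mortality is a listed outcome, pneumonia-related death counts against cure, and an independent committee reviews safety. This stands in the main. Seeing mortality does not correct the other estimates, however, and a 5-point excess could pass as chance. With 276 per arm and an assumed 28% against 33%, SE = √((0.28 × 0.72 + 0.33 × 0.67)/276) = 0.039, so the 95% interval is about ±7.7 points.

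Fourth, total DDDs per patient is a legitimate measure of what was consumed. Agreed; it should stay, but not be read alone.

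It is also tempting to say that day-7 scores exist only for patients still in the ICU, or that patients in the ICU at day 28 have no end date. The article does not establish either. The assessment schedule is in an additional file not shown, and it is unclear whether the day-28 limit covers discharge as well as death.

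**Conclusion.** The point holds in limited form. For total DDDs by day 21, the false-benefit direction follows from the definition itself. For ICU stay it depends on an unstated convention: it is present if death ends the stay and much smaller, about 0.1 day, if only patients discharged alive are compared, at the price of conditioning on survival. For day-7 organ dysfunction the issue is survivor selection, with a small illustrated shift; the documents do not support a claim that harm would show there as a material benefit.

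The size, 0.3 to 0.9 days and 0.3 to 1.0 DDDs per patient for 5 points of excess early mortality, rests wholly on assumed inputs. It is modest, but its sign is wrong. The trial's success criterion uses only the two co-primaries, and these are untouched. The change should be made, but it does not threaten the main conclusions.

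**What to change.** Fix the following before analysis, since the analysts are not blinded:

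- **ICU stay:** analyse time to ICU discharge alive with death as a competing event. Report cumulative incidence by arm, with administrative censoring at the end of follow-up.
- **Antibiotic use:** keep total DDDs by day 21 and report DDDs per day alive to day 21 beside it, with mortality next to both this result and ICU stay. Neither measure suffices alone. At an assumed 1.3 DDDs per day, a death on day 3 contributes a low total (3.9) but a high rate (1.3 per day alive). A survivor treated for 12 days contributes 15.6 DDDs, or 15.6/21 = 0.74 per day alive.
- **Day-7 organ dysfunction:** state how deaths and ICU discharges before day 7 enter the comparison, and add a sensitivity analysis that ranks death worst. This is one option among several.

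The dates, deaths and antibiotic data needed are already due to be collected, so the cost is wording and some extra standard analysis. The downside is that the results are less direct to read than a mean difference.
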